## Abstract

**Background:**

Use of Botulinum toxin-A (BoNT-A) for treatment of upper limb spasticity in children with cerebral palsy has become routine clinical practice in many paediatric treatment centres worldwide. There is now high-level evidence that upper limb BoNT-A injection, in combination with occupational therapy, improves outcomes in children with cerebral palsy at both the body function/structure and activity level domains of the International Classification of Functioning, Disability and Health. Investigation is now required to establish what amount and specific type of occupational therapy will further enhance functional outcomes and prolong the beneficial effects of BoNT-A.

**Methods/Design:**

A randomised, controlled, evaluator blinded, prospective parallel-group trial. Eligible participants were children aged 18 months to 6 years, diagnosed with spastic hemiplegic cerebral palsy and who were able to demonstrate selective motor control of the affected upper limb. Both groups received upper limb injections of BoNT-A. Children were randomised to either the modified constraint-induced movement therapy group (experimental) or bimanual occupational therapy group (control). Outcome assessments were undertaken at pre-injection and 1, 3 and 6 months following injection of BoNT-A. The primary outcome measure was the Assisting Hand Assessment. Secondary outcomes included: the Quality of Upper Extremity Skills Test; Pediatric Evaluation of Disability Inventory; Canadian Occupational Performance Measure; Goal Attainment Scaling; Pediatric Motor Activity Log; modified Ashworth Scale and; the modified Tardieu Scale.

**Discussion:**

The aim of this paper is to describe the methodology of a randomised controlled trial comparing the effects of modified constraint-induced movement therapy (a uni-manual therapy) versus bimanual occupational therapy (a bimanual therapy) on improving bimanual upper limb performance of children with hemiplegic cerebral palsy following upper limb injection of BoNT-A. The paper outlines the background to the study, the study hypotheses, outcome measures and trial methodology. It also provides a comprehensive description of the interventions provided.

**Trial Registration:**

ACTRN12605000002684

## Background

Cerebral palsy is "a group of permanent disorders of the development of movement and posture causing activity limitation(s) that are attributed to non-progressive disturbances that occurred in the developing fetal or infant brain" [[1], p. 9]. Secondary to the brain disturbance, children with cerebral palsy often experience neurological symptoms including dystonia, ataxia, athetosis and particularly spasticity [2]. Spasticity occurs as a result of a loss of upper motor neuron inhibition on the lower motor neurons which results in increased or impaired motor unit firing and altered muscle tone [2]. Muscle spasticity is characterised by a velocity-dependent increase in tonic stretch reflexes (muscle tone) with exaggerated tendon jerks (phasic stretch reflex) resulting from hyperexcitability of the stretch reflex [3]. Adding to these neurological symptoms, skeletal muscle morphology in children with cerebral palsy is also altered due to abnormally long muscle sarcomere lengths and muscle tissue containing a hypertrophic extracellular matrix of poor quality [2,4]. This results in muscle stiffness affecting posture and movement and can be described as hypertonia or increased muscle tone [3].

Hemiplegic cerebral palsy, characterised by a clinical pattern of unilateral motor impairment, accounts for 35.1% of all cerebral palsy types in Victoria, Australia [5], 15.3% in Ontario, Canada, 40% in Sweden [6] and 31.2% in North England, United Kingdom [7]. Along with muscle spasticity and hypertonia, children with hemiplegic cerebral palsy experience a loss of upper motor neurone excitation that is typically associated with poor selective motor control and weakness, and in some instances, sensory deficits. These additional impairments significantly impact on a child's ability to perform daily tasks [8-11].

The spastic motor type of cerebral palsy is the most common, comprising about 80% of all reported cases [12]. Although the mechanism is unknown, spastic muscle often shortens to create muscle contractures, which often leads to fixed deformity and further functional complications [13]. Therefore, management of the upper limb in children with cerebral palsy usually involves a variety of interventions targeting the musculoskeletal system. These may include splinting and casting, passive stretching, the facilitation of posture and movement (e.g. occupational therapy and physiotherapy) or systemic spasticity-reducing medication and surgery [14]. Botulinum toxin-A (BoNT-A) is now commonly used as an adjunct to these interventions.

### Botulinum toxin-A in the treatment of the upper limb in children with cerebral palsy

BoNT-A is a powerful neuromuscular paralysing agent that is produced by the anaerobic bacterium *clostridium botulinum *[15]. BoNT-A acts at the neuromuscular junction by inhibiting the release of the neurotransmitter *acetylcholine*. Injection of BoNT-A into selected muscles produces dose-dependent chemical denervation resulting in reduced muscle activity. The denervation is temporary as sprouting of new nerve terminals from the treated nerves leads to re-innervation. The function of the original terminal is eventually restored leading to the recovery of the affected muscles [16]. The period of clinically useful relaxation appears to be 12-16 weeks [12]. The aim of BoNT-A in the treatment of the upper limb in children with cerebral palsy is to produce selective reduction in muscle spasticity using the smallest possible dose. The reduction in spasticity is intended to provide an opportunity to optimise the effects of motor training by reducing the negative interference of spasticity. It can also serve to improve tolerance and compliment the effects of splinting and casting potentially delaying the need for soft tissue surgery [9].

Use of BoNT-A for the treatment of upper limb spasticity in children with cerebral palsy has become routine clinical practice in many paediatric treatment centres worldwide. In Australia, injection of BoNT-A (Botox(r) only) is now an approved and government funded treatment for moderate to severe spasticity of the upper limbs children with cerebral palsy, 2 to 17 years of age inclusive [17]. A recent Cochrane review, including ten randomised controlled trials predominantly of high quality, provided high-level evidence that BoNT-A in the upper limb, in combination with occupational therapy, improved outcomes at both the body function/structure and activity level domains of the International Classification of Functioning, Disability and Health (ICF) [18] when compared to occupational therapy alone, BoNT-A alone or no treatment [19]. The review authors concluded that injection of BoNT-A in the upper limb in children with cerebral palsy should always be accompanied by planned post-injection therapeutic intervention. This conclusion is consistent with a recently developed international collaboration documenting upper limb BoNT-A evidence-based guidelines for intervention and follow-up for children with cerebral palsy [20].

Intramuscular injection of BoNT-A results in relaxation of the affected muscle providing a window of opportunity for maximising therapy outcomes. For children with hemiplegia however, injection of BoNT-A alone does not improve the ability of the child to use the affected limb and clinical experience suggests attempts to use the limb immediately following injection often remain effortful, inefficient and result in clumsy movement. Persistent verbal and physical encouragement by therapists and parents may frequently lead to further frustration and negative or defiant behavior. Therapy must, therefore, create the opportunity, motivation, experience and environment in which a child can learn how to use their affected limb to maximize the effectiveness of the BoNT-A.

A recent systematic review of all upper limb interventions in children with cerebral palsy found that occupational therapy in combination with BoNT-A produced the largest treatment effect of all upper limb interventions on activity level outcomes [21]. Despite high-level evidence supporting occupational therapy post-injection, no clinical trial has specifically investigated the optimal type and amount of therapy following BoNT-A. Approaches undertaken in recent trials however, all point to the effectiveness of bursts of therapy focused on specific skill acquisition or goal achievement [22-26]. Further investigation is required to establish what intensity and/or specific type of therapy will enhance functional outcomes and prolong the beneficial effects of BoNT-A [14].

### Movement-based therapies in the upper limb

For occupational therapists, bimanual occupational therapy training (BOT) in children with hemiplegia is a commonly applied intervention. Theories of practice have previously been described in the literature [27-29], although clinical service delivery is eclectic and potentially covers a range of interventions. An essential element of the bimanual approach to upper limb training includes the repetitive practice of motivating, meaningful and purposeful bimanual activities (i.e. occupations). This has been well supported by recent advances in the areas of neuroscience, basic mechanisms of hand function and more specifically, motor control and motor learning theories [30]. Although this approach is commonly used and has strong theoretical foundations, it has not been systematically defined and empirically investigated.

In 2007, Gordon and colleagues comprehensively described and evaluated a bimanual approach to upper limb training in children with hemiplegic cerebral palsy called Hand Arm Bimanual Intensive Training (HABIT) [31]. Despite similarities with BOT, specific differences exist between the therapies. HABIT includes: high intensity of treatment (6 hours per day for 2 weeks); the use of behavioural shaping theory [32]; and relies solely on environmental adaptation for grading of activities, rather than physical assistance or handling of the child ([name], personal communication). Children participating in HABIT demonstrated improved bimanual upper limb function compared with a group receiving customary care [31]. However, the promising evidence provided by this small trial of moderate methodological quality suggests that further investigation of bimanual intervention in children with hemiplegia is both justified and warranted [28].

Constraint-induced movement therapy (CIMT) has been adopted as a method of teaching a child to use his/her affected upper limb through use of a restraint on the non-affected limb and massed practice of movements of the affected limb [33]. It has been proposed as an effective way of improving outcomes following upper limb BoNT-A injection, particularly as it removes the need for persistent prompting [34]. It may, on the other hand, lead to the opposite effect if a child demonstrates adverse behavioral responses to the restraint [33].

*Developmental disregard *is a term used to describe a child with hemiplegia who may disregard, or learn not to use, the affected limb during the development of motor function [35]. Children with even mild impairment in the affected limb learn effective strategies to manage daily tasks (e.g. play) with one hand, discovering that performance is more efficient using only the non-affected hand [10]. Constraint-Induced Movement Therapy (CIMT), aims to reverse the behavioral suppression of movement in the affected upper limb by constraining use of the non-affected limb and providing massed practice of activities with the affected limb [36]. Studies in adults following stroke have provided evidence of adaptation in the brain involving the motor cortical areas controlling movement of the more affected limb following CIMT [37-39]. Since the potential for central nervous system plasticity in young children is increased relative to adults [40-42], it is postulated that this approach might prove to be especially effective in children [43].

CIMT is a multi-faceted intervention and studies describing its use in children with cerebral palsy present wide variation in its application in relation to: method of restraint; length of restraint (per day, number of weeks); type and duration of therapy; intervention environment (that is home, school, or clinic) and intervention provider (therapist, parent, or teacher). Children included in studies have also varied in age, diagnosis, severity of motor and sensory impairment, cognitive abilities and behavior. Despite the emerging popularity of CIMT in children with hemiplegic cerebral palsy, a Cochrane review [44] identified a significant treatment effect in only a single trial which adopted a less intensive modified form of CIMT [8]. The modified CIMT (mCIMT) involved the application of a restraint on the unaffected upper limb and less than three hours per day of therapy provided to the affected limb [44]. While a positive trend was found favoring CIMT [35] and Forced Use [45], no significant treatment effect was demonstrated for these interventions when compared with traditional services.

Studies published to date have provided limited evidence of factors that may impact on the effectiveness of CIMT. Response to CIMT does not appear to be age-dependent and children with more impaired bimanual hand function demonstrate greater improvement than less impaired children [8]. Although not statistically significant, trends have also been reported as favoring children with cortical/subcortical lesions compared to those with periventricular white matter lesions [8]. More recently, Kuhnke et al., [46] reported that adolescents and young adults with ipsilateral corticospinal projections responded differently to CIMT intervention in comparison to those with contralateral projections. Although these findings must be interpreted cautiously due to methodological limitations [47], the study by Kuhnke et al., [46] adds information about children's potential responses to CIMT.

There is currently no published trial directly comparing a BOT protocol with a CIMT protocol. However, in 2008 Gordon and colleagues [48] published data from a quasi-randomised trial of 16 children with hemiplegic cerebral palsy that compared a one-on-one uni-manual approach to treatment (CIMT) versus a one-on-one bimanual approach to treatment (HABIT) [48]. This small trial reported similar changes for both groups on outcomes including the Jebsen-Taylor Test of Hand Function, Assisting Hand Assessment and accelerometry. The finding, measured using the Assisting Hand Assessment, indicated immediate post-treatment improvements in upper limb bimanual performance using either a uni-manual or bimanual approach to training. However, retention of gains was not examined following either intervention.

## Methods/Design

The aim of this current paper is to describe the methodology of a randomised controlled trial comparing the effects of modified constraint-induced movement therapy (a uni-manual therapy) versus conventional bimanual occupational therapy on improving bimanual upper limb performance of children with hemiplegic cerebral palsy following upper limb injection of BoNT-A. Bimanual upper limb performance, assessed using the Assisting Hand Assessment, was selected as the primary measure as the central aim of all upper limb motor-based interventions in children with hemiplegia is to improve a child's actual use of their affected upper limb in a range of daily tasks, including those requiring bimanual performance; rather than what they can do in a clinical setting or how normal their movement appears. This RCT builds on the existing evidence supporting the use of BoNT-A in the upper limb of children with cerebral palsy. It aims to identify the most effective intervention following injection of BoNT-A. A further aim is to explore the individual characteristics of children that impact on response to treatment. Finally, it will also provide additional evidence regarding dose response to treatment, specificity of training effects, and the retention of treatment effects.

### Primary objective

To compare the effects of modified CIMT versus bimanual occupational therapy (BOT) in improving the bimanual performance of children with hemiplegic cerebral palsy following upper limb BoNT-A injection.

#### Hypothesis 1

Modified CIMT is more effective than conventional BOT in improving the bimanual performance of children with hemiplegic cerebral palsy following upper limb BoNT-A injection.

#### Hypothesis 2

Relative to baseline performance on the Assisting Hand Assessment, modified CIMT results in greater retention of gains in bimanual performance compared with BOT.

### Secondary objectives

A. To compare the effect of modified CIMT versus bimanual occupational therapy (BOT) on secondary outcomes relating to: the performance of activities of daily living; the quality of upper limb movement; occupational performance; individual goal achievement; and frequency of use of the affected upper limb of children with hemiplegic cerebral palsy following upper limb BoNT-A injection.

#### Hypothesis 3

Modified CIMT is more effective than conventional BOT in improving performance of activities of daily living, quality of upper limb movement, occupational performance, individual goal achievement and frequency of use of the affected upper limb in children with hemiplegic cerebral palsy following upper limb BoNT-A injection.

B. To evaluate the clinical significance of change identified on the primary outcome, the Assisting Hand Assessment.

#### Hypothesis 4

That changes on the Assisting Hand Assessment associated with intervention are of a clinically significant magnitude. Clinical significance was defined as a change score of more than 5 raw score points (2.6 logits) on the AHA ([name], personal communication).

C. To evaluate the impact of age and actual treatment dosage on the primary outcome, the Assisting Hand Assessment.

#### Hypothesis 5

Younger children (irrespective of treatment type) will show greater improvement in bimanual performance following uni-manual or bimanual therapy and upper limb BoNT-A injection.

#### Hypothesis 6

Children who undertake treatment of greatest intensity (irrespective of treatment type) will show greater improvement in bimanual performance.

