#### Testing the effectiveness of therapy (Hypotheses 1 and 2)

Using continuous, interval level data from the AHA, differences between the two groups were assessed using a linear regression approach to analysis of covariance (ANCOVA). This controlled for the covariates of baseline AHA scores and the child's age. These variables were included as covariates as they might provide alternative explanations for any observed changes in scores. The size of treatment effect was estimated by comparing differences in group means and their 95% confidence intervals. Regression analyses and scatter-plots were used to investigate the relationship of post-treatment outcome with initial deficit.

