#### Testing the effect of age and intensity of therapy (Hypotheses 5 & 6)

Data related to the number of minutes spent by all children undergoing treatment was extracted from the log book for each child. Associations between the intensity of therapy and outcome and age of children and outcome were determined, while controlling for the covariate of group, using ANCOVA.

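### Hypothesis 6 is offered as dose-response evidence, but it rests on therapy minutes that were not assigned within either arm and are adjusted for group alone

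*Protocol article*

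**What the plan says.** The Methods/Design section lists among the trial's aims that "it will also provide additional evidence regarding dose response to treatment". Secondary objective C is worded causally: "To evaluate the impact of age and actual treatment dosage on the primary outcome, the Assisting Hand Assessment". Hypothesis 6 follows from it: "Children who undertake treatment of greatest intensity (irrespective of treatment type) will show greater improvement in bimanual performance".

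The analysis is given under Testing the effect of age and intensity of therapy (Hypotheses 5 & 6). The exposure is time actually spent: "Data related to the number of minutes spent by all children undergoing treatment was extracted from the log book for each child". The model is then described: "Associations between the intensity of therapy and outcome and age of children and outcome were determined, while controlling for the covariate of group", by ANCOVA. Group is the only covariate named. For Hypotheses 1 and 2 the protocol names more: "This controlled for the covariates of baseline AHA scores and the child's age".

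Movement-based therapy: General Considerations sets the amounts. Both arms have two clinic sessions a week of 45 to 60 minutes for 8 weeks. The mCIMT arm has one home target of 3 hours a day, 7 days a week. The BOT arm is encouraged to practise at home, with no time set.

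**The concern.** Minutes completed are known only after randomisation and are not allocated by the trial. Two children in the same arm differ in minutes because of the child, the family, or how therapy was going. If whatever sets the minutes also influences AHA change, the coefficient mixes any effect of practice time with that influence. Adjusting for group cannot separate the two, because the selection happens within each arm.

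The Background says further work is needed to establish what intensity of therapy improves outcome. A positive Hypothesis 6 would be read as an answer and could inform decisions about therapy amounts. A null result could equally be read as showing that amount does not matter. The analysis supports neither conclusion.

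**Working it through.** **1. What the minutes coefficient can rest on.** Scheduled clinic time is 2 × 8 = 16 sessions, or 16 × 45 = 720 to 16 × 60 = 960 minutes, in both arms. The mCIMT home target is 3 × 60 × 7 × 8 = 10,080 minutes for every child; the BOT home target is none. The only assigned contrast in amount is therefore between arms, where it coincides with therapy type. Putting group in the model removes that contrast. What remains is unassigned variation within arms.

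**2. Inputs.** The protocol gives no sample size or power figure for Hypothesis 6, so there is nothing to reproduce. N = 34 and N = 40 come from the Sample Size section, where they serve the primary comparison. I take the outcome to be AHA change, following the word improvement in the hypothesis. The correlations below are assumptions; the protocol gives none.

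**3. Model.** Minutes have no effect. One unmeasured factor U has within-arm correlation a with minutes and b with AHA change:
- minutes = group term + a·U + √(1−a²)·noise
- change = b·U + √(1−b²)·noise

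The implied within-arm correlation of minutes with change is a × b. The test is the plan's: change on group and minutes, two-sided 5%, with 5,000 simulated trials per setting.

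| a = b | a × b | Significant, N = 40 | Significant, N = 34 |
|---|---|---|---|
| 0 | 0 | 4.8% | 5.0% |
| 0.3 | 0.09 | 8.1% | 7.7% |
| 0.5 | 0.25 | 33% | 29% |
| 0.6 | 0.36 | 62% | 55% |
| 0.7 | 0.49 | 89% | 85% |

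From 0.5 upward almost every significant result is in the hypothesised direction.

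**4. Check by hand, N = 40.** With one covariate, z = atanh(a × b) × √(40 − 4) = atanh(a × b) × 6, and the rate is about P(Z > 1.96 − z) + P(Z < −1.96 − z).
- 0.09: z = 0.0902 × 6 = 0.54; rate 0.078 + 0.006 = 8%.
- 0.25: z = 0.2554 × 6 = 1.53; rate P(Z > 0.43) = 33%.
- 0.36: z = 0.3769 × 6 = 2.26; rate P(Z > −0.30) = 62%.

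These agree with the simulation.

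**5. When it does not happen.** With only one link present (0.5 and 0), the rate stays at about 5%. Both links are needed.

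**6. Direction.** With correlations of 0.5 and −0.5 and N = 40, the unadjusted model is significantly negative in 34% of trials. This case is not fanciful. The Background cites a trial in which more impaired children improved more; if such children also practised less, a real dose effect could be masked.

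**7. What adjustment buys (N = 40).** If the common cause is baseline AHA itself (0.5 and 0.5), adding it lowers the rate of a false positive association from 34% to 2.7%, close to the nominal 2.5% in that direction. If the common cause is unrelated to baseline AHA and age, adding both leaves the rate at 34%.

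**The case against.** The analysis section already speaks of associations, and Hypothesis 6 refers to children who undertake more treatment. On that view the plan claims nothing causal. This is fair to the analysis section, but not to the aim and the objective, which speak of dose response and impact. The wording has to be reconciled.

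A reader might go further and infer that children who cope badly or respond poorly stop the programme earlier, so that the analysis is bound to favour Hypothesis 6. The protocol does not say so. The Background says only that CIMT may "lead to the opposite effect if a child demonstrates adverse behavioral responses to the restraint", with nothing about minutes. The sections on frustration, distraction and task avoidance concern behaviour within tasks and sessions, and mostly describe how the therapist kept the child working. Clinic sessions have a set number and length. The shared cause is therefore plausible, not documented, and its sign is open.

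The size is equally open. At correlations near 0.3 the inflation is small, and the larger rates need an unmeasured factor with strong links to both minutes and outcome. That objection stands, and the figures should be read as a range over assumptions.

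Finally, this is a secondary hypothesis, and the randomised comparison does not depend on it.

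**Conclusion.** The point holds as a mismatch between claim and analysis. The plan promises dose-response evidence from an exposure that is unassigned within arms, adjusted for group only. With no true effect, the chance of a significant result at N = 40 runs from the nominal 5% with no shared cause, through about 8% at 0.3 and 33% at 0.5, to 62% at 0.6. This assumes one unmeasured factor with equal correlations with minutes and AHA change. With opposite signs, a true effect could be hidden instead. The argument does not depend on how accurately minutes were logged, and it does not show that any bias occurred. Hypotheses 1 and 2 are untouched. It merits correction because the remedy is cheap and changes what may be concluded.

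**What to change.** **Wording.** In Methods/Design and in secondary objective C, replace the dose-response and impact language with an exploratory, non-randomised association between completed therapy time and AHA outcome. State that no conclusion about therapy dose will be drawn from it. Carry the same description into Hypothesis 6.

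**Analysis.** Keep the pooled, group-adjusted model and add age and baseline AHA. As a sensitivity analysis use the 1-month AHA, which falls at about the start of therapy and so reflects early response to BoNT-A before practice begins. State that these covariates remove only confounding through themselves, not through tolerance, cooperation or response during therapy.

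**Two additions to avoid.**
- Excluding children who stopped early, and reading a vanished association as proof of selection, does not work. Early stoppers are the low-minute children, so power falls whatever the cause. In a simulation with N = 34 that dropped the lowest quarter of minutes in each arm (an assumption), significance vanished in 56% of significant positive results under a true dose effect with within-arm correlation 0.36. It also vanished in 56% under pure confounding of the same size. Stopping early is also undefined for BOT home practice, which has no time requirement.
- Separate fits in arms of about 17 have roughly 30% power at a correlation of 0.36, against about 55% pooled.

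**Cost.** A few sentences and a few extra covariates, using data already collected; the article says analysis was still under way. The price is a weaker secondary claim.
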